Although many reviews of VR interventions have shown positive improvements in stroke rehabilitation, most studies have focused on the impact of VR intervention-based rehabilitation on the treatment of dysfunction, and only a few studies have focused on changes in the central nervous system in stroke patients under VR intervention. With high spatial resolution, fMRI might detect patterns of brain excitation during motor work or rest by using the blood oxygen level-dependent signal as an alternative indicator of neural activity, but the precision of fMRI is restricted. EEG technology detects electrical activity for the purposes of providing enhanced efficiency data and identifying critical neural substrates that underlie certain functional deficits. In the examination of patients with stroke, quantitative EEG measures demonstrated not only clinical value but also multidimensional repeatability and reliability (19). The use of multimodal neuroimaging to obtain more comprehensive, rich, accurate, and reliable brain information provides new monitoring means for the description of neural dynamic processes (20). Neuroimaging techniques could indirectly describe angiogenesis and neuroplasticity and provide quantifiable indicators and responses to therapeutic interventions for stroke (21). Synchronous EEG-fMRI could simultaneously collect electrophysiological and blood oxygen metabolism signals in brain activities, combining the advantages of the two, which not only provides the feasibility of fusion for the study of the two modes (22) but also provides a new means for understanding the description of neural dynamic processes, which plays an irreplaceable role. Therefore, the primary goal of this study is to explore the effects of VR intervention on upper extremity motor function and associated brain activation in stroke patients. Multimodal neuroimaging characteristics that could be used as indicators of a better response to VR were also investigated.

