## Methods and analysis

### Design and setting

This is a prospective, randomized controlled trial conducted by the Second Hospital of Jiaxing. A total of 78 patients who meet the inclusion and exclusion criteria will be randomly divided into two groups. The intervention group will receive VR training and conventional rehabilitation treatment, and the control group will receive conventional rehabilitation treatment only. All treatments will be provided five times per week for 4 weeks. The primary outcome is the degree of restored upper extremity motor function, which is evaluated by the Fugl-Meyer Assessment Upper Extremity Scale (FMA-UE). Secondary outcomes are neuroimaging outcomes, which are measured by resting-state functional magnetic resonance imaging (rs-fMRI), task-state functional magnetic resonance imaging (ts-fMRI), and electroencephalography (EEG). All outcomes will be evaluated at baseline and weeks 4 and 8. The study's flow chart is shown in Figure 1. The Standard Protocol Items: Recommendations for Interventional Trials (SPIRIT) checklist (23) is detailed in an additional document available upon request (Supplementary material), and the schedule of this study is shown in Table 1.

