### Data analysis

Data analysis will be performed using SPSS software (IBM, Statistics 25 version). Measurement data that follow a normal distribution as a whole will be expressed as mean ± standard deviation (X ± SD), and the whole data will not follow a normal distribution in median (interlude spacing) [M(P25–P75)]. The count data will be expressed as the number of cases (composition ratio) [*N*, (%)], and the analysis is tested by the *X*^2^ or Fisher's exact tests precisely. The comparison between the groups will be carried out by the *t*-test or the Mann–Whitney *U*-test based on whether the measurement data present a normal distribution and homogeneous variance to compare the differences in FMA-UE and independent sample *t*-test for the parameter in FIM, BI, grip strength, fMRI and EEG at a *p*-value below 0.05. There are no interim analyses planned.

fMRI image processing will use the statistical parameter graph software statistical parametric mapping (SPM)12. Before data processing, all data will be adjusted in orientation; and then head-action alignment, high-resolution structural image, and the average functional image will be registered; the high-resolution structural image after registration will be split; all the aligned functional images will be standardized to the Montreal Neurological Institute space using the standardized parameters generated during the segmentation process; the standardized voxel size is 3 mm × 3 mm × 3 mm; and the standardized functional image is spatially smoothed. Through an intragroup analysis, a paired *t*-test will be performed to assess brain alterations in each group (before and after the treatment). Age and gender will be taken into account as variables in the data analysis. The association between the improvement value of the correlation scales and the change in fMRI image data will be examined using the Pearson correlation coefficient.

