For pre-processing and analysis, EEG data will be exported to MATLAB 9.2.0 (MathWorks, Inc., Natick, MA). A second-order Butterworth filter with a bandpass of 0.1–70 Hz and a band stop of 49–51 Hz will be used to filter the data. The data will be divided into 90 segments of 2 s each, and epochs with obvious artifacts will be removed by visual inspection. To find and eliminate non-physiological artifact components, data will be subsequently subjected to an independent component analysis using the EEGLAB rapid independent component analysis (ICA). The missing channels will be interpolated after the artifacts will be removed. The frequency domain indicators will be extracted and counted, Fourier transform on the preprocessed data will be performed and converted into a power spectral density (PSD) in decibels, each frequency band of interest will then be exported, the power value will be calculated, statistical analysis will be performed, and the difference will be output into the document.

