In this study, the FMA-UE score will be used to explore the behavioral changes of VR intervention combined with conventional rehabilitation training to improve the motor function of the upper extremities on the hemiplegic side. As previously stated, VR-based exercise therapy may help improve FMA-UE, allowing patients to engage more actively in the activities daily of living while also demanding less support from healthcare professionals or caretakers. In order to predict stroke early, the regional reconstruction of cerebral cortex function and activation of brain regions with quantitative parameters is evaluated and the correlation between the application value and motor function of combined metabolic functional imaging index and electroencephalographic imaging index in the evaluation of stroke patients before and after VR rehabilitation is explored. The upper extremity motor function of patients will be provided with quantitative indicators, trying to find out the patient group with potential benefits of rehabilitation therapy and guide the clinical practice of reasonable and effective VR rehabilitation therapy.

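### The specified correlation of scale improvement with fMRI change describes mechanism, but cannot support the subsidiary aim of showing who responds to VR

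*Protocol article*

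**What the plan says.** The aim appears in two places in the protocol article. The end of the Introduction, after the primary goal, adds: "Multimodal neuroimaging characteristics that could be used as indicators of a better response to VR were also investigated". The last paragraph of the Discussion speaks of "trying to find out the patient group with potential benefits of rehabilitation therapy" and of guiding clinical practice accordingly.

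The Data analysis section specifies these imaging analyses:

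- Between-group t-tests on the fMRI and EEG parameters.
- Within-group comparison before and after treatment: "a paired *t*-test will be performed to assess brain alterations in each group".
- The link to clinical outcome: "The association between the improvement value of the correlation scales and the change in fMRI image data will be examined using the Pearson correlation coefficient". The section does not say whether this is done in the VR arm, in each arm or in both arms combined.
- Covariates: "Age and gender will be taken into account as variables in the data analysis". It is not said which analyses this covers.
- For EEG, after the power values are calculated: "statistical analysis will be performed, and the difference will be output into the document". No link to clinical response is described.

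The Discussion also mentions exploring "the correlation between the application value and motor function of combined metabolic functional imaging index and electroencephalographic imaging index", again as a correlation.

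**The concern.** An indicator of who responds to VR has to meet two conditions. It must be available before treatment is chosen, and it must be related to the difference between VR and control, not merely to how much a patient improves. A correlation between two changes meets neither condition. The fMRI change needs a scan at week 4 or 8, and a patient who would have recovered equally well under control treatment contributes to the correlation exactly as a patient helped by VR does.

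What is at stake is interpretation. A significant correlation could be reported as a marker of VR response when it shows only that brain and function recover together. The randomised control arm, which is what allows the two to be told apart, would go unused for this aim.

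**Working it through.** The plan attaches no figure to this correlation, so there is nothing to reproduce. The check has three parts.

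**1. Aim against analysis**

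| Needed to say who responds to VR | Specified analysis |
|---|---|
| Marker known before treatment | fMRI change, known at week 4 or 8 |
| Contrast of VR with control | None in the correlation |
| Multimodal marker (Introduction) | fMRI only; EEG enters only the loosely worded correlation in the Discussion |

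Table 1 of the article schedules FMA-UE, both fMRI types and EEG at baseline and weeks 4 and 8 for all patients, so the data for a direct test will exist in both arms.

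**2. How the specified test behaves**

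Inputs from the article (Sample size): 78 enrolled and 15% dropout, so 78 × 0.85 = 66.3, or about 66 analysed. The effect size f = 0.25 corresponds to d = 2f = 0.5 for two groups. The significance level is 0.05, taken as two-sided. Inputs assumed, because the article gives none: the shared-recovery correlation and the size of any effect modification. Each scenario used 5,000 simulated trials, 1:1 allocation and a 0.5 SD arm difference in FMA-UE change.

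*Scenario A: no marker modifies the VR effect; clinical and fMRI change share general recovery (r = 0.5 in both arms).* Percentage significant:

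| Test | N = 66 | N = 78 |
|---|---|---|
| Pearson, VR arm | 86.7 | 90.8 |
| Pearson, control arm | 86.5 | 91.9 |
| Pearson, pooled | 98.5 | 99.5 |
| Baseline marker × arm | 4.4 | 4.7 |

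*Scenario B: a baseline marker truly modifies the VR effect; the two changes are unrelated.* The Pearson test, in either arm or pooled, rejects in 4.2% to 5.5% of trials, which is the nominal level. The power (%) of the interaction test is:

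| Modifier (residual SD per marker SD) | N = 66 | N = 78 |
|---|---|---|
| 0.5 | 49.8 | 56.2 |
| 0.75 | 82.2 | 87.5 |
| 1.0 | 96.3 | 98.5 |

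So the correlation can be positive when nothing predicts response to VR, and uninformative when something does.

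Precision of the interaction, in residual SDs of the outcome per marker SD with equal arms: SE = 2/√N. For N = 66 this is 2/√66 = 0.246. The 95% CI half-width is 1.96 × 0.246 = 0.48, and the slope detectable with 80% power is 2.8 × 0.246 = 0.69. For N = 78 the detectable slope is 2.8 × 2/√78 = 0.63.

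**3. Pooling, if it were done**

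With equal arms, zero correlation within each arm, and arms differing by d SD on both changes:

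pooled r = (d²/4) / (1 + d²/4)

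- d = 0.5: 0.0625/1.0625 = 0.06
- d = 0.8: 0.16/1.16 = 0.14
- d = 1.0: 0.25/1.25 = 0.20

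The pooled correlation detectable with 80% power is tanh(2.80/√(N − 3)): 0.34 for N = 66 and 0.31 for N = 78. At the article's own effect size the artefact is small by comparison.

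**The case against.** The strongest reply is that the Data analysis section never says the Pearson correlation serves the response-indicator aim. It fits the main aim, which concerns the effect of VR on motor function and the associated brain activation, and for that purpose it is an ordinary descriptive choice. This stands: the sentence is not wrong in itself.

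A reader might go further and infer that this is the only analysis planned for the aim, so that the trial cannot answer its own question. The article does not support that. It is condensed, a fuller protocol or analysis plan may contain a predictor model, and the Discussion mentions a further correlation with a combined imaging and EEG index. That wording is loose enough to include pre-treatment values, but it is still a correlation and brings in no comparison with control.

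The aim is also modest. It is absent from the Abstract and from the design and outcome sections. The Discussion refers to benefit from rehabilitation therapy, not from VR specifically, and elsewhere describes imaging as a way to follow progress and adjust training. For monitoring, a correlation between changes is relevant. Even so, the wording about finding the patient group that may benefit points to selection, and the Introduction names response to VR.

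A reader might also infer that pooling the arms will manufacture a correlation. The article does not say the arms are pooled, and at its own effect size the artefact is about 0.06.

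Finally, an interaction test here is weak: about 50% power for a modifier of 0.5 SD with 66 patients. That is a reason to label it exploratory, and it also makes rewording the aim a legitimate alternative.

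**Conclusion.** The point holds as a mismatch between a subsidiary aim and the imaging-to-response analysis the article specifies. The correlation can describe how imaging change and functional change go together. It cannot support a statement about who responds to VR as opposed to who recovers in general, because it uses post-treatment information and makes no comparison with control.

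The reasoning on timing and contrast needs no assumed numbers. The rejection rates in Scenario A rest on an assumed shared-recovery correlation of 0.5, and those in Scenario B on assumed modifier sizes; they illustrate the problem and do not predict this trial's results. The pooling artefact is secondary and conditional.

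Nothing here touches the primary FMA-UE comparison or the between-group imaging tests. This is a cheap improvement that should be made, and it does not threaten the trial's main result.

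**What to change.** Keep the Pearson correlation, label it descriptive, and state that it is done within each arm or as a partial correlation adjusted for arm.

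Then choose one of two routes for the response-indicator aim:

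1. **Analyse it.** Name a few baseline markers in advance, for example one fMRI measure of M1 activation or laterality and one EEG power measure. Fit FMA-UE at a named follow-up visit on baseline FMA-UE, arm, marker and marker × arm. Report the interaction with its 95% CI, labelled exploratory.
2. **Reword it.** Limit the statements in the Introduction and Discussion to the association between imaging change and functional change.

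The first route costs a few sentences and a few regressions on data already scheduled in both arms. Its drawback is imprecision: with about 66 patients the interval is roughly ±0.48 SD of outcome per marker SD, so a null result would exclude only large modifiers. The second route costs only wording, but gives up the question of who benefits.

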### Quality control

The reasons for the suspension of the study and the relationship between the clinical study should be carefully recorded, and the criteria for the suspension of clinical research should be stipulated. When the subject will suspend the clinical study, the corresponding clinical evaluation will be carried out, and the statistical processing principle of the data after the suspension of the clinical study will be determined. For the subject who proposes to withdraw from the clinical study in the middle, the reason should be clearly recorded, if the subject will not be followed up on time, the reason should be consulted by telephone or letter, and the situation after the study will be investigated, and the clinical evaluation of the subject when withdrawing from the clinical study will be carried out.

In order to make this project function smoothly, the relevant operating procedures of clinical research and the implementation process will be scientifically and rigorously standardized. Researchers will be trained uniformly to master the implementation of interventions in the intervention group and the control group so as to improve the internal observation consistency and observer-to-observer consistency of researchers and ensure the reliability of clinical research conclusions. Quality monitors will be set up to carry out quality control and supervision of the whole process of research, the records and reports of all research data will be checked and confirmed, and the correctness and completeness of the case report will be formed, and it will be ensured that they are consistent with the original data. The trial review team consists of two staff members from the review department and will be responsible for a regular review of progress, authenticity, and safety every 12 weeks. Trial audit teams, independent data monitoring, and ethics committees must review the conduct throughout the trial.

## Discussion

Extensive studies have been published demonstrating the effectiveness of VR training and related therapies in enhancing upper motor function, with combination therapy appearing to be more beneficial (32, 33). Furthermore, they continue to have a limited scope, focusing just on the effectiveness without delving into the process. Based on our prior research, the neuroplasticity hypothesis, and real-world experience, VR training could be a multimodal therapy to induce cortical reorganization in stroke patients.

At present, no accepted theory could explain the neural mechanism of VR to promote motor function recovery, and the study of interhemispheric inhibition models has been relatively perfect (34), but alternative models and related influencing factors, such as synaptic regeneration ability, still have large research space in patients with various stages of stroke (35). VR is a rehabilitation treatment technology with great development potential, with the deepening of research study and the rapid development of technology, and it is likely to occupy a larger application space and a more important position in stroke upper extremity rehabilitation. Therefore, the underlying neural mechanisms of the impact of VR use on stroke rehabilitation still need to be further studied. How VR induces activation in adjacent cortical regions and whether the brain could produce effective synapses through motor learning and high-intensity training need further verification.

Research by Garcia et al. (36) showed that VR training effectively promoted the functional remodeling of the brain. Some studies have also found that VR training can activate the motor cortex, cerebellar cortex, and frontal white matter areas of the patient's contralateral side (37, 38). When completing virtual activities, visual and auditory feedback can enhance the motivation and focus of the participants, thereby improving the patient's attention and spatial perception function (39). By repeating the virtual activity task, the participants' motor learning ability and executive function can be strengthened (40). In addition, studies have confirmed that exercise training itself can also promote the recovery of cognitive function in patients after stroke, and the reason may be that exercise can promote the growth and survival of neurons in the affected side of the brain (41). A total of two studies reported clinical outcomes of improved upper extremity motor function after VR rehabilitation, with higher fractional anisotropy (FA) in the ipsilateral corticospinal tract (CST) and transcallosal motor fibers in a bilateral arm training study (42) and increased bilateral sensorimotor cortex and hippocampal gray matter volume in a constraint-induced movement therapy study (43). A previous study of patients with subacute stroke showed an initial decrease in FA in the ipsilateral CST and transcallosal M1–M1 fibers in the early post-stroke period (44).

A single modality of neuroimaging has been unable to meet the needs of researchers, who hoped to achieve multimodal observation of the brain by integrating information from both temporal and spatial aspects of the brain. Neurological imaging tended to obtain information from multiple modalities and integrate them and combined with different advantages of modal imaging technology so as to obtain more comprehensive, rich, accurate, and reliable brain information, and this method also provides a new monitoring method for the description of the cognitive neural dynamic process (45). VR-associated neurophysiological changes can be assessed by non-invasive and portable neuroimaging techniques including fMRI (46) and/or EEG (47) to determine changes in cerebral hemodynamic responses or oscillating brain waves, respectively. In particular, the use of fMRI as a measure of cerebral hemodynamic response to the neurological rehabilitation process has received attention. In addition, EEG has long been used to measure brain activity levels during cognitive or motor tasks and in a variety of clinical populations. The cortical activation measurements in fMRI and EEG or functional near-infrared spectroscopy (fNIRS) techniques show a high degree of correlation between motor and cognitive tasks (48, 49). Above all, valid methodologies to correlate objective functional measures that are valid and repeatable are the brain plasticity measure techniques using the EEG. The previously stated techniques can help rehabilitation specialists fully comprehend how such a patient's temporal and spatial neural plasticity keeps changing after VR intervention, allowing them to track the progress of patients in recovery, ascertain their reactions, and adjust the training modules to fit their unique program. The ability of fMRI and EEG to detect changes in neurophysiological measurements can provide feedback on where and how well the brain is activated, and clinical researchers can use this feedback to set treatment intensity and adjust the next treatment plan. Therefore, observing neurological defects of M1 through fMRI and EEG is of certain significance to explore the mechanism of VR in the treatment of stroke.

In this study, the FMA-UE score will be used to explore the behavioral changes of VR intervention combined with conventional rehabilitation training to improve the motor function of the upper extremities on the hemiplegic side. As previously stated, VR-based exercise therapy may help improve FMA-UE, allowing patients to engage more actively in the activities daily of living while also demanding less support from healthcare professionals or caretakers. In order to predict stroke early, the regional reconstruction of cerebral cortex function and activation of brain regions with quantitative parameters is evaluated and the correlation between the application value and motor function of combined metabolic functional imaging index and electroencephalographic imaging index in the evaluation of stroke patients before and after VR rehabilitation is explored. The upper extremity motor function of patients will be provided with quantitative indicators, trying to find out the patient group with potential benefits of rehabilitation therapy and guide the clinical practice of reasonable and effective VR rehabilitation therapy.

